### Testing Considerations

All equipment and testing facilities will be perfume-free (or as low as possible) as many people with ME/CFS also report multiple chemical sensitivities. Testing facilities will provide footstools and beds to rest. Rest periods will be provided at the request of the participant during the testing sessions to reduce fatigue. Paper questionnaires can be sent home with participants to be completed at their own time and mailed back to spread the effort. Cambridge Neuropsychological Test Automated Battery testing can be paused at one point to allow a rest period. Breakfast/food will be provided after the fasting bloods have been taken.

### Analysis Plan

Exit questionnaires will be audiorecorded, transcribed verbatim, and sent back to participants for member checking. Themes will be extracted and summarized from interview transcripts.

Analysis of continuous data to assess preliminary evidence of benefit will include examination of mean differences and confidence intervals ranging from 75% to 95%. Regression analysis will be used to explore preliminary evidence of a relationship between allostatic load and physical activity. The alpha level will be set at 0.2, an appropriate level for a pilot studies [32]. Categorical questionnaire data will be analyzed using chi-square analysis. As this study is a pilot study, any inferential statistics will be purely exploratory (ie, not powered to detect statistical differences).

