**Methods:**

This study will use a mixed method design, with a 3-arm pilot randomized controlled trial, exit interviews, and collection of feasibility and process data. A total of 30 adults with ME/CFS will be randomized to receive either (1) pacing, (2) pacing and conventional physical activity, or (3) pacing and active video gaming. The intervention duration will be 6 months, and participants will be followed up for 6 months postintervention completion. The intervention will be conducted in the participant’s home, and activity intensity will be determined by continuously monitored heart rate and ratings of perceived exertion. Feasibility and acceptability and process data will be collected during and at the end of the intervention. Health-related outcomes (eg, physical activity, blood samples, quality of life, and functioning) will be collected at baseline, end of intervention, and 6 months after intervention completion.

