### Intervention

After baseline assessment, participants will be block randomized (block size = 6, 1:1:1 allocation ratio) into pacing only, pacing plus conventional physical activity, or pacing plus active video gaming (Figure 1).

Participants will be randomized using a computer-generated random number sequence and opaque sealed envelopes generated by a University of South Australia researcher not involved in the study. All participants will receive telephone support from the research assistant once a week for the first 3 months of the intervention and every 2 weeks for the last 3 months of the intervention, and participants can contact the research assistant at any additional time. At the end of the 12 months, participants still enrolled will be provided with an Xbox Kinect unit in acknowledgement of their participation.

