### Sample Size

This is the first study to investigate the feasibility and acceptability of active video gaming to increase the physical activity levels of people living with ME/CFS. A sample of 30 participants was deemed appropriate to provide the process feedback regarding testing procedures, and feasibility and acceptability data will be collected from 10 participants regarding the active video gaming experience.

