### Health-Related Outcomes

#### Overview

There will be at least 4 weeks between effort testing and commencement of the intervention with 2 weeks being stable at a pretest pattern of symptoms/activity. Participants may require longer recovery before commencing the intervention.

All health-related outcomes will be measured at 3 time points: baseline, 6 months after baseline at the end of the intervention, and at 6-month follow-up after the intervention has been completed. In addition, accelerometer, inclinometer, and continuous captured HR will be measured during week 6, week 12, and week 18 of the intervention. The Karnofsky Scale [25] will be collected more frequently, with the research assistant recording the Karnofsky Scale value each time telephone contact is made with a participant.

Health-related outcomes have been chosen after extensive consultation with the stakeholder advisory group which included people living with ME/CFS. Outcomes have been selected to first provide data on the primary health-related outcomes (ie, physical activity and allostatic load:11 variables). Outcomes have also been selected to cover client-centered outcomes such as use of time, quality of life, and functioning. These outcomes are of utmost importance to the people with ME/CFS and capture the broader International Classification of Functioning, Disability, and Health framework concepts of activity limitations and participation restriction [26]. Finally, outcomes have been selected to capture the vast range of symptoms reported by people with ME/CFS to ensure the levels are monitored alongside the physical activity changes to ensure safety and investigate net benefit to the participants.

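### The arm comparison is described as mean differences with no stated baseline adjustment, although every health outcome is measured at baseline and arms have only 10 participants each

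*Protocol article*

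**What the plan says.** The Analysis Plan section of the protocol article gives the method for continuous outcomes as follows: "Analysis of continuous data to assess preliminary evidence of benefit will include examination of mean differences", together with confidence intervals at levels from 75% to 95%. It does not say whether these are differences in follow-up means, in change from baseline, or in baseline-adjusted means. Regression is named only for the relation between allostatic load and physical activity, and chi-square for categorical questionnaire data. The section adds "The alpha level will be set at 0.2, an appropriate level for a pilot studies" and that "any inferential statistics will be purely exploratory (ie, not powered to detect statistical differences".

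Under Health-Related Outcomes, the Overview schedules all health-related outcomes at baseline, at the end of the 6-month intervention and 6 months later. It also says "accelerometer, inclinometer, and continuous captured HR will be measured during week 6, week 12, and week 18 of the intervention". The Intervention section places randomization after the baseline assessment and states "participants will be block randomized (block size = 6, 1:1:1 allocation ratio"; no stratification factor is mentioned. The abstract says "A total of 30 adults with ME/CFS will be randomized", and the Sample Size section says "feasibility and acceptability data will be collected from 10 participants regarding the active video gaming experience".

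**The concern.** The effectiveness contrasts serve the first two hypotheses: video gaming against pacing alone, and video gaming against conventional activity. Their estimates are among the data meant to guide later effectiveness trials. With 10 people per arm and simple blocking, sizeable chance differences in baseline activity are likely. The baseline value is collected before randomization, so it is a legitimate covariate, yet the stated method gives it no role.

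An unadjusted follow-up difference would leave part of any chance imbalance in the estimate and give a wider interval than the data allow. A change-score difference would use the baseline but overcorrect for it whenever r is below 1. The three readings of a mean difference therefore give different estimates and interval widths, and the article does not choose between them.

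**Working it through.** **Inputs from the article.** N = 30, allocated 1:1:1, so 30/3 = 10 per arm (five blocks of 6). This agrees with the 10 video gaming participants in the Sample Size section. That section gives no effect size, SD or power, so there is no further figure to reproduce.

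**Assumptions.** r, the correlation between the baseline and follow-up values of an outcome, is not in the article; 0.3 to 0.7 is used. SDs are taken as equal at baseline and follow-up, the relation as linear, and data as complete. All results are in SD units.

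**1. Unadjusted contrast of follow-up means.** SE = √(2/10) = 0.447. With 27 degrees of freedom, the half-width is 0.53 for a 75% interval and 0.92 for a 95% interval.

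**2. Chance baseline imbalance.** The baseline difference between two arms has the same SE, 0.447. P(|difference| > 0.5) = 2 × [1 − Φ(0.5/0.447)] = 2 × [1 − Φ(1.118)] = 0.264, or 26%. For at least one of the three pairs of arms, simulation gives about 50%.

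**3. Effect of a 0.5 SD imbalance on the estimate.**
- Follow-up means: expected shift r × 0.5, which is 0.15, 0.25 and 0.35 SD at r = 0.3, 0.5 and 0.7. The last two are about half to two-thirds of the 75% half-width (0.25/0.53 and 0.35/0.53).
- Change scores: expected shift (r − 1) × 0.5, in the opposite direction, which is −0.35, −0.25 and −0.15 SD.
- ANCOVA: no expected shift if the model is right.

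**4. Precision.** For three arms and one covariate, the ANCOVA variance is (1 − r²) × (2/10) × (1 + 1/25). The last factor is the small-sample penalty, 1 + 1/(30 − 3 − 2) = 1.04. The change-score variance is 2(1 − r) × (2/10).

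| r | SE, follow-up means | SE, change | SE, ANCOVA | ANCOVA vs follow-up means | ANCOVA vs change |
|---|---|---|---|---|---|
| 0.3 | 0.447 | 0.529 | 0.435 | −3% | −18% |
| 0.5 | 0.447 | 0.447 | 0.395 | −12% | −12% |
| 0.7 | 0.447 | 0.346 | 0.326 | −27% | −6% |

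The 95% half-width falls from 0.92 to 0.89, 0.81 and 0.67 SD. Against follow-up means, the equivalent number per arm is 10/[(1 − r²) × 1.04] = 10.6, 12.8 and 18.9.

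**5. What the week 6, 12 and 18 device data can add.** With complete data, a repeated-measures model with unstructured covariance and a separate baseline effect at each visit uses the same regressors at every visit. Its end-of-intervention arm effects therefore equal those from ANCOVA at that visit. A simulated data set of 30 people gave identical coefficients. These visits help in two other situations: when 6-month values are missing, or when the target is the average over the intervention. For the baseline-adjusted mean of weeks 6, 12, 18 and month 6, under compound symmetry and without the penalty factor, the variance is [(1 + 3r)/4 − r²] × (2/10). This gives SEs of 0.277, 0.274 and 0.239 at r = 0.3, 0.5 and 0.7. That is a different estimand from the end-of-intervention contrast.

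**The case against.** The best defence has four parts.

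- **The wording is open.** The text says the analysis will include mean differences, which is not exclusive and also fits change from baseline or adjusted means. The hypotheses speak of increasing activity, which suits change scores at least as well as follow-up means. A reader might infer that the plan fixes a raw end-visit comparison; the article does not say so. This stands. What remains is that the article names a method for each type of question, gives regression only to allostatic load, and leaves open a choice that changes the estimate. ANCOVA is narrower than both alternatives over the range examined.
- **A condensed article may leave covariates to an analysis plan that is not shown.** This also stands, and limits the point to improving the stated method. It is not evidence that the trial will analyse its data without adjustment.
- **The gain rests on an assumed r.** Activity here is symptom-contingent and may be stopped, reduced or progressed, which could lower r. At r = 0.3 the gain over follow-up means is only 3%.
- **The contrast is secondary, exploratory and unpowered, and the sample was chosen for feasibility.** Randomization keeps the unadjusted difference unbiased on average, so the 26% figure shows conditional shift, not bias. This limits the weight of the point. But where estimates and intervals are the product, their precision still matters.

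A reader might also infer that leaving out the interim device data leaves baseline imbalance uncorrected, or that people lost after those visits contribute nothing. The documents support neither. The interim values come after randomization and cannot correct baseline imbalance, and no section states a complete-case end-visit analysis.

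**Conclusion.** The point holds as a worthwhile improvement to a secondary, exploratory analysis. The article names mean differences without baseline adjustment where the baseline value is available for every health outcome and arms are 10 each. The 26% chance of an imbalance above 0.5 SD for a given pair depends only on the arm size and approximate normality of the arm means. The precision gain depends on r, which is assumed: small at 0.3 against follow-up means and substantial from about 0.5. The documents do not show that the trial will use raw differences, that the contrast is biased, or that the interim device data would sharpen the end-of-intervention contrast when data are complete.

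**What to change.** State in the Analysis Plan that each continuous outcome is compared in one three-arm model adjusted for its own baseline value (ANCOVA), reporting video gaming versus pacing and video gaming versus conventional activity with the planned 75% to 95% intervals. The cost is one degree of freedom and slightly more analysis work, with no new data. When the article appeared, baseline testing had not begun, so the choice could be fixed before any outcome was seen.

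Optionally, for device-measured activity, specify a baseline-adjusted mixed model that includes weeks 6, 12 and 18, and say what it is for: missing 6-month values or a time-averaged contrast. Its cost is higher, because arm-by-visit terms and a covariance structure must be estimated from 30 people.

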## Results

A 6-month extensive consultative protocol development phase has been completed; 3 comprehensive rounds of protocol topics, comments, and plans for amendment occurred.

The first round focused on the following general topics: inclusion criteria, time frame between effort testing and intervention commencement, time and frequency of assessment, and the inclusion of continuous HR data collection. The Karnofsky Scale and alternative disability scales were discussed. The second round included discussion on the following broad topics: design modification to 3-arm trial, symptom history data collection, and the pacing and physical activity protocol. The third round involved discussion on the following topics: AEs protocol, adherence diary, and clarification of maximal and submaximal effort test procedures.

Virtual meetings allowed for interactive group discussion, and consensus was reached on all aspects of the protocol. All members of the stakeholder advisory group have endorsed the current protocol. Enrollment began in January 2017; as of publication, 12 participants were enrolled. Baseline testing is scheduled to commence in mid-2017.

## Discussion

### Summary

The proposed research will fill gaps in the existing literature by (1) providing only the second known study of symptom-contingent pacing as a strategy to increase physical activity in adults with ME/CFS, (2) providing the first data on feasibility and acceptability of using active video games as a strategy to increase physical activity in people with ME/CFS, and (3) providing longitudinal data regarding the relationship between allostatic load and physical activity in people living with ME/CFS.

Adults living with ME/CFS often suffer orthostatic intolerance, and as such, a physical activity modality that can be achieved in a sitting or reclining position is advantageous. In addition, many people living with ME/CFS report short bouts of activity to be easier to manage, hence an activity modality that allows short bouts of several minutes to then allows adequate rest addresses the consumer requirements. Active video games such as Nintendo WiiFit and Xbox Kinect have been demonstrated to demand low to moderate levels of physical activity in the elderly, even when sitting [18]. So playing these games while sitting/reclining/lying can still be useful. Active video gaming has been shown to be feasible and acceptable to other chronic health populations such as those with cerebral palsy and stroke and is commonly played sitting in these populations [17].

Evidence suggests active video gaming can improve the health and well-being of people with a variety of chronic and debilitating health conditions [17]. Despite the evidence to suggest active video gaming as effective and relevant, no studies have investigated the effect, feasibility, or acceptability of active video gaming in adults with ME/CFS.

### Conclusion

The results of this trial will provide the feasibility and acceptability data to suggest whether active video gaming can be pursued as a strategy to help people living with ME/CFS overcome physical inactivity. The pilot study will provide important data to guide future effectiveness trials and is intended to deliver safe, effective, evidence-based, consumer-driven physical activity interventions to the ME/CFS community.

## Abbreviations

AE: adverse event
AL: allostatic load
BMI: body mass index
CRP: C-reactive protein
GET: Graded Exercise Therapy
HDL: high-density lipoprotein
HR: heart rate
HRV: heart rate variability
LDL: low-density lipoprotein
ME/CFS: myalgic encephalomyelitis/chronic fatigue syndrome
NSAE: nonserious adverse event
RPE: ratings of perceived exertion
VT: ventilatory threshold
